# Glossary

STEMI ST elevation myocardial infarction

MEA Multiple electrode analyzer

ECG Electrocardiogram

PPCI Primary percutaneous coronary intervention

PCI Percutaneous coronary intervention

CRF Case report form

ADP Adenosine di-phosphate

BHI Bristol Heart Institute

UFH Unfractionated heparin

GPI Glycoprotein 2b/3a Receptor Inhibitor

MACE Major adverse cardiac events

ASPI Arachidonic acid activation assay

AUC Area under curve

TIMI Trials in myocardial infarction

P2Y12 Specific ADP platelet receptor

A&E Accident and emergency

UHBristol University Hospitals Bristol NHS Foundation Trust

CRP C-reactive protein

eGFR Estimated glomerular filtration rate

CCU Coronary Care Unit

PIS Patient information sheet

CTEU Clinical Trials and Evaluation Unit

ECG Electrocardiogram

ARC Academic research consortium

GUSTO Global Use of Strategies to Open Coronary Arteries

# Definitions

STEMI Determined by a 12-lead ECG at the time of presentation with/without chestpain demonstrating either 1mm ST elevation in two contiguous leads or new-onset left bundle branch block.

Low platelet response Determined by comparison of ADPtest result from multiplate analyzer against a reference population of patients receiving aspirin and a P2Y12 receptor inhibitor, defined by Sibbing et al (ref). The lowest quintile (20%) of the population were identified to have significantly increased risk of adverse thrombotic events (i.e. stent thrombosis).

MACE A composite of target vessel and target lesion revascularization, cardiac death, and non-fatal myocardial infarction.

Stent thrombosis Using the Academic Research Consortium (ARC) definition(1) events are defined as definite, probable or possible and early (0-30days), late (31-360days) or very late (>360days). Definite stent thrombosis must be confirmed by angiographic or autopsy evidence of thrombosis/vessel occlusion. Probable stent thrombosis is defined as unexplained death within 30days of the index procedure, or evidence of acute myocardial infarction involving the target vessel territory. Possible stent thrombosis is classified as all unexplained death occurring at least 30days from the procedure.

Bleeding Using the GUSTO bleeding score(2) where events are classified as severe (deadly bleeding; intracerebral bleeding or substantial hemodynamic compromise requiring treatment), moderate (requiring transfusion) or mild (bleeding not requiring transfusion or causing hemodynamic compromise).

# Lay Summary

Heart attacks are increasingly being treated with immediate re-opening and placement of a metal-mesh tube (stent) in the blocked heart artery. In addition to scaffolding the artery with a stent, drugs are used to thin the patient’s blood. We have recently changed the drugs given to patients presenting to the Bristol Heart Institute with heart attacks. The drugs we have selected are potent blood thinners and have been shown to act very fast.

In this study we want to measure the level of blood thinning achieved at the end of the stenting procedure. We believe that there may be a variable response to the blood thinning drugs and patients with a low response may be at increased risk of blood clotting problems. We will describe the relationship between the measure of blood thinning at the end of the procedure with the time given for the drug to take effect and ultimately with complications developed within the first 30 days following the stenting procedure.

# Background

Optimal treatment of acute ST-elevation myocardial infarction (STEMI) involves rapid diagnosis, and transfer to a percutaneous coronary intervention (PCI)-capable cardiac centre for immediate mechanical revascularisation (3).

The primary-PCI (PPCI) service in Bristol is co-ordinated by the Bristol Heart Institute (BHI). Following a recent expansion of our catchment, incorporates the Gloucestershire, Avon & Wiltshire territories of the local network, we anticipate over 600 PPCI cases in the next year. We are achieving excellent results and our purpose-built unit allows rapid transfer of patients to the catheterisation laboratory with a median ‘door to balloon time’ of 39minutes, far exceeding the national average (median time 50minutes) (4).

Platelet activation occurs early in the cascade of events leading to coronary arterial occlusion and STEMI. Therefore anti-platelet therapy is fundamental to successful re-canalisation and subsequent reperfusion of the myocardium. In light of the ‘time-critical’ nature of STEMI treatment, current anti-thrombotic therapy involves use of both intravenous and oral agents to confer both immediate and long-term anti-thrombotic effects.

Significant advances in the inhibition of platelet activity have occurred in recent years and current data supports the use of increasingly potent anti-thrombotic agents and platelet inhibitors to limit the risk of future cardiac events including mortality. However, increasingly potent and advanced pharmacotherapy comes at a financial cost and at a cost of an increased risk of complications, particularly bleeding. A balance has to be achieved between effective suppression of thrombosis, prevention of significant bleeding and cost.

We have recently amended our anti-thrombotic protocol in the treatment of STEMI - converting from using un-fractionated heparin (UFH) with glycoprotein 2b/3a receptor inhibitors (GPI) to bivalirudin monotherapy in the catheter laboratory, with additional substitution of prasugrel for clopidogrel. Prasugrel is administered to patients on arrival at the Bristol Heart Institute prior to undertaking angiography and PPCI. Use of bivalirudin has been shown to offer equivalent benefit in terms of limiting major adverse cardiac events (MACE), with a reduction in cardiac mortality and bleeding vs UFH plus GPI (5). Prasugrel is a potent inhibitor of the platelet ADP receptor P2Y12. It was tested against clopidogrel in the TRITON-TIMI 38 trial and demonstrated a significant reduction in a composite of cardiac mortality, non-fatal myocardial infarction and non-fatal stroke in the treatment of STEMI (6).

The use of prasugrel and bivalirudin in the acute treatment of STEMI offers excellent anti-platelet and anti-thrombotic effect (5,6). The combination of prasugrel with bivalirudin should confer increased protection against early thrombotic events, as prasugrel has been demonstrated to offer faster inhibition of platelet activity vs clopidogrel (7). However, it should be noted that the HORIZONS-AMI trial, assessing bivalirudin vs. UFH/GPI, revealed an increased rate of stent thrombosis at 24hours with bivalirudin monotherapy. Reassuringly, at 30 days the stent thrombosis rate was not statistically different in both treatment groups (8). This transient early negative outcome with bivalirudin most likely relates to the pharmacokinetics of the drug, and the protocol of administration. Bivalirudin is administered intravenously, with an initial bolus (0.75mg/kg) and then an infusion (1.75mg/kg/h) until the completion of the angiography/PCI procedure. Bivalirudin has a half-life of ≈25minutes and, therefore, thrombin activity is restored fairly rapid when the infusion stops. The increase in acute stent thrombosis may signal a gap in anti-thrombotic protection arising from the waning anti-thrombin effect of bivalirudin and the increasing anti-platelet effect of prasugrel on the P2Y12 receptor inhibitor.

The newly amended BHI anti-thrombotic protocol assumes that all STEMI patients will achieve adequate platelet inhibition with prasugrel by the time bivalirudin is stopped, immediately after treatment with a coronary stent. The validation of this assumption in’real’ STEMI patients has not been tested. This is the aim of the study.

# Hypothesis and Study Objectives

Minimising the time from STEMI symptom onset to definitive treatment, with mechanical revascularisation, remains a major focus of attention in optimising the PPCI service. We hypothesise that continued reductions in the “door to balloon” time (time from hospital admission to achieving an open artery in the catheter laboratory) may result in some patients undergoing PPCI with incomplete P2Y12 blockade, leading to an increase in risk of early thrombotic events. We speculate that the rapid restoration of coronary flow achieved with PPCI may offer inadequate time to achieve platelet inhibition with prasugrel, prior to the loss of the anti-thrombin effect of bivalirudin.

The primary objective of the study is to describe variation in platelet activity at the end of the PPCI and to quantify the relationship between “door to balloon time” and platelet function in the first 24 hours after completing the PPCI.

The secondary objective of the study is to test the hypothesis that patients with high platelet activity at the time of arrival at hospital (baseline) achieve less platelet inhibition in the first 24 hours following commencement of anti-thrombotic and anti-platelet therapy.

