## Sample size and justification

The primary analysis will be a mixed model regression (see below). Calculation of the sample size needed to detect a statistically significant effect of a key predictors in such analyses require the following assumptions to be defined (parameter = estimate):

r-squared for full model = 0.25

r-squared for reduced model (excluding key predictor) = 0.20

number of predictors in full model = 8

number of predictors being tested = 1

Because two key predictors will be tested (see below), a significance level of 0.025 will be adopted (Bonferroni correction) giving a nominal hypothesis test at p<0.05 for each predictor. For 80% power, the above assumptions require a target sample size of 135. This target sample size needs to be further adjusted by the relative efficiency of the analysis, i.e. to take into account the three repeated measures. Estimating the relative efficiency requires further assumptions about the correlations between the repeated measures; for correlations ranging from 0.5 to 0.8, the relative efficiency varies from 1.25 to 1.50. Taking the lower estimate of relative efficiency gives a final target sample size of 108 (i.e. 135/1.25).

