## Analysis plan

The primary analysis will be a mixed model regression to take into account the three repeated measures of platelet function at 1, 2 and 24 hours after completion of PPCI. Platelet function on arrival at the hospital, and platelet function after completion of PPCI, are not expected to be influenced by door-to-balloon time and will be entered as covariates. Other potential confounding factors influencing platelet function (e.g. peak troponin, age, gender, diabetic status) will also be entered as covariates. Two key predictors will be tested in the model, namely the effects of (a) door-to-balloon time and (b) platelet function on arrival at the hospital.

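### Arrival platelet function is secondary in section 6 but takes half the alpha in 7.5 and 7.6; Holm would hold the same 5% and never reject less than the plain Bonferroni split

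*Protocol*

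**What the plan says.** Protocol section 6 (Hypothesis and Study Objectives) sets two levels of objective. The primary one is to describe variation in platelet activity at the end of the procedure and "to quantify the relationship between “door to balloon time” and platelet function in the first 24 hours after completing the PPCI". The next level concerns arrival platelet function: "The secondary objective of the study is to test the hypothesis that patients with high platelet activity at the time of arrival at hospital (baseline", and so on, to the expectation that such patients achieve less inhibition over 24 hours.

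Section 7.6 (Analysis plan) gives the primary analysis, one mixed model, two tests with no order between them: "Two key predictors will be tested in the model, namely the effects of (a) door-to-balloon time and (b) platelet function on arrival at the hospital".

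Section 7.5 (Sample size and justification) sets the level: "Because two key predictors will be tested (see below), a significance level of 0.025 will be adopted (Bonferroni correction". The same sentence continues "giving a nominal hypothesis test at p<0.05 for each predictor". The sample size is computed for one predictor at a time from "r-squared for full model = 0.25" and "r-squared for reduced model (excluding key predictor) = 0.20", with 8 predictors in the full model. It gives 135 for 80% power, then 108 after dividing by a relative efficiency of 1.25.

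**The concern.** A hypothesis that section 6 calls secondary takes half of the alpha in the primary analysis and so helps to set the sample size. Door-to-balloon time is tested at 0.025 whatever the arrival result, because plain Bonferroni passes no alpha on when one of the two tests succeeds.

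The same two-test family can be held at 5% by Holm's step-down rule. Holm rejects everything that Bonferroni rejects and sometimes more. At stake is power on the study's main question at a fixed number of patients, and a clear statement of how the arrival hypothesis ranks. Type I error is not at stake: the present rule controls it.

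**Working it through.** **Inputs, all from section 7.5.** R-squared 0.25 (full) and 0.20 (reduced); 8 predictors; 1 tested; alpha 0.025; unadjusted n 135; relative efficiency 1.25 to 1.50. Sidedness is not stated, so I take a 1-df partial F test, which is equivalent to a two-sided t test.

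**Formula.** f² = (0.25 − 0.20)/(1 − 0.25) = 0.0667. Power is P(F′ > F crit), where F′ is noncentral F with 1 and n − 9 degrees of freedom and noncentrality f² × n.

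**The plan's own figure.** At n = 135 the noncentrality is 0.0667 × 135 = 9.0.
- At alpha 0.025, power is 76.7%; 80% needs n = 146.
- At alpha 0.05, power is 84.5%; 80% needs n = 120.

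The stated 135 for 80% therefore does not reproduce from the stated inputs. The step 135/1.25 = 108 is correct. The baseline below is 76.7%, which differs from the protocol's 80%.

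**Full gain from 0.025 to 0.05, n held fixed.**

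| Setting | Power at 0.025 | Power at 0.05 | Difference (points) |
|---|---|---|---|
| n = 135 | 76.7% | 84.5% | 7.9 |
| 108 patients, efficiency 1.25 | 76.4% | 84.4% | 8.0 |
| 108 patients, efficiency 1.50 | 84.2% | 90.2% | 6.0 |
| Starting from the stated 80% (normal approximation) | 80.0% | 86.9% | 6.9 |

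**Gain under Holm.** Door-to-balloon time is rejected if its p-value is below 0.025, or if it is below 0.05 and the arrival p-value is below 0.025. With independent tests, and q the power of the arrival test at 0.025:

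power = 0.7669 + q × (0.8454 − 0.7669)

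| Arrival test | q | Door-to-balloon power | Gain (points) |
|---|---|---|---|
| No effect | 0.025 | 76.9% | 0.2 |
| 30% power | 0.30 | 79.0% | 2.4 |
| 50% power | 0.50 | 80.6% | 3.9 |
| Equal power | 0.767 | 82.7% | 6.0 |
| Certain to reject (ceiling) | 1 | 84.5% | 7.9 |

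The arrival test gains in the same way, with the roles exchanged.

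**Fixed sequence, for comparison.** Door-to-balloon time is tested first at 0.05, so its power is 84.5%. Arrival platelet function is tested at 0.05 only if the first test succeeds.
- Both effects real and of the assumed size, tests independent: arrival power is 0.8454 × 0.8454 = 71%, against 76.7% under Bonferroni.
- No door-to-balloon effect: arrival power is 0.05 × 0.8454 = 4%.

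**Family-wise error, independent tests, both nulls true.**
- Bonferroni: 1 − 0.975² = 0.049.
- Holm: the same 0.049, because its first rejection needs a p-value below 0.025.
- Fixed sequence: 0.050.
- Both tests at 0.05 with no gate: 1 − 0.95² = 0.0975.

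**The case against.** The strongest reply is that nothing is broken. Bonferroni is a valid rule, the sample size was computed at 0.025, and including a secondary test in the split is conservative. One model of one outcome can serve both objectives. The protocol also leaves expansion of the analyses to a later statistical analysis plan. Most of this stands: the cost is power forgone, not an error and not a departure from the plan's own budget. The appeal to a later plan is weaker, because the protocol does not leave the rule open. It fixes Bonferroni and bases the sample size on it.

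A reader might infer three stronger things that the documents do not support.

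- *That the split costs a flat 6 to 8 points.* That is the whole step from 0.025 to 0.05. Only a fixed sequence, or an arrival test almost certain to reject, delivers it. The protocol gives no figure that puts the arrival test near certainty. Its correlations of 0.5 to 0.8 concern the three repeated outcome measures, and the end-of-procedure value entered as a covariate may absorb some of the tracking from arrival to later values.
- *That Bonferroni buys no error control.* That is so only against Holm or a gated sequence. Against two ungated tests at 0.05 it roughly halves family-wise error.
- *That section 6 dictates a fixed sequence.* It ranks objectives but states no testing order. Its primary objective is worded as description and quantification, and only the secondary one as a hypothesis test. A fixed sequence would gate the latter behind the former.

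**Conclusion.** The point holds as an avoidable inefficiency together with an inconsistency of rank. Section 6 makes arrival platelet function secondary, while 7.5 and 7.6 make it an equal partner under plain Bonferroni. At an effective n of 135, replacing that rule with Holm raises door-to-balloon power from 76.7% by between 0.2 and 7.9 points, depending on the power of the arrival test. In the equal-power case it reaches 82.7%. Family-wise error stays within 5% and neither test loses power.

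The figures assume a 1-df effect, the protocol's R-squared values and, for Holm, independent tests. They do not cover the interaction between door-to-balloon time and time after the procedure that the Primary Outcomes section describes. The failure of 135 to reproduce is a separate matter. It lowers the baseline here but is not caused by the alpha split.

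**What to change.** In sections 7.5 and 7.6, replace plain Bonferroni with Holm for the two key predictors: compare the smaller p-value with 0.025 and, only if it is significant, the other with 0.05. Give arrival platelet function one status throughout sections 6, 7.5 and 7.6, either as a joint primary hypothesis or as a secondary one. In the same edit, replace the wording "giving a nominal hypothesis test at p<0.05 for each predictor", which is unclear beside a 0.025 level, with the Holm rule.

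The cost is wording only, with no extra patients or data. Holm's guarantee of 5% needs no assumption about the correlation between the tests. A fixed sequence is a possible alternative, but it trades away arrival-test power as shown above and is not the recommended change.

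### The secondary objective speaks of less inhibition, but the planned test asks whether the arrival level predicts the later level, so a positive result would not show less inhibition

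*Protocol*

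**What the plan says.** The section Hypothesis and Study Objectives sets the secondary objective as a test that "patients with high platelet activity at the time of arrival at hospital (baseline) achieve less platelet inhibition in the first 24 hours" after treatment starts.

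The Analysis plan (7.6) specifies a "mixed model regression to take into account the three repeated measures of platelet function at 1, 2 and 24 hours after completion of PPCI". The outcome is therefore the level at each time. Two key predictors are tested, "namely the effects of (a) door-to-balloon time and (b) platelet function on arrival at the hospital". The arrival and end-of-PPCI levels, the plan says, "are not expected to be influenced by door-to-balloon time and will be entered as covariates". No null value other than no effect is given.

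The Sample size section gives each key predictor its own controlled test: "a significance level of 0.025 will be adopted (Bonferroni correction"). It arrives at 108 patients and assumes correlations between repeated measures of 0.5 to 0.8.

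Inhibition is nowhere defined as a change or a percentage. The nearest definition, of low platelet response in the Definitions section, rests on a single on-treatment result: "Determined by comparison of ADPtest result from multiplate analyzer against a reference population of patients receiving aspirin" and a P2Y12 inhibitor.

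**The concern.** The objective, in its ordinary sense, compares how far treatment lowers platelet activity in patients who start high and patients who start low. The planned coefficient does not measure that. A slope of zero between later and arrival levels is not the value that means equal inhibition. If every patient falls by the same amount, the slope on the true arrival level is 1. If every patient loses the same percentage, the slope equals the fraction that remains, which is positive. A positive slope is what would be read as support for the hypothesis, yet it is expected when inhibition is identical in everyone.

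The end-of-PPCI level is a second problem. The Background section has prasugrel given on arrival, before angiography, so this value is already on treatment and lies within the 24-hour window of the objective. Holding it fixed takes out whatever arrival effect has appeared by then.

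At stake is what one of the study's two alpha-controlled tests can conclude.

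**Working it through.** **The plan's own figure.** 135/1.25 = 108 is correct. The 135 itself does not reproduce: f² = (0.25 − 0.20)/(1 − 0.25) = 0.0667 with one of eight predictors tested, level 0.025 and 80% power gives 146. That is a separate matter, and 108 is used below as planned.

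**Inputs from the protocol.** n = 108; level 0.025 (sidedness is not stated, two-sided assumed); eight predictors, taken as arrival level, end-of-PPCI level and six others; three later measurements; correlations 0.5 to 0.8.

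**Assumptions not in the protocol.** Normal errors; reliability ρ of the arrival value equal to the stated correlation; the other six covariates independent; complete data. With patient-level covariates, testing the mean of the three later values is then equivalent to a random-intercept mixed model.

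**Model.** The true arrival level has variance 1. Measurement error has variance s² = (1 − ρ)/ρ. Each later true level is k times the arrival level, minus a constant. k = 1 is equal absolute inhibition; k < 1 with no constant is equal percentage inhibition with fraction k remaining. Let P = 1 + 1/s² + k²/s². Then:

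- slope on arrival, adjusted for end-of-PPCI: b = (k/s²)/P
- residual variance of the three-visit mean: v = k²/P + s²/3
- variance of arrival given end-of-PPCI: w = 1/ρ − k²/(k² + s²)
- SE = √(v/(99w)), with 108 − 9 = 99 degrees of freedom and critical t 2.276

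**Equal absolute inhibition (k = 1).**

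- ρ = 0.5: s² = 1, b = 1/3 = 0.333, v = 0.333 + 0.333 = 0.667, w = 2 − 0.5 = 1.5, SE = √(0.667/148.5) = 0.067, b/SE = 4.97. Rejection is 99.6%; simulation gave 99.7%.
- ρ = 0.65 and 0.8: simulation gave 99.9% and 100%.
- ρ = 0.2, below the protocol's range: b = 0.167, v = 2.0, w = 4.8, SE = √(2/475.2) = 0.065, b/SE = 2.57. Rejection is 62%; simulation gave 61%.

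The nominal rate is 2.5%. Mean simulated slopes at ρ = 0.5 to 0.8 were +0.34 to +0.45 with the end-of-PPCI value in the model, and +0.50 to +0.80 without it.

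**Equal percentage inhibition, end-of-PPCI in the model, assay noise unchanged (simulated rejection).**

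| Activity remaining | ρ = 0.5 | ρ = 0.8 |
|---|---|---|
| 50% | 98% | 100% |
| 30% | 81% | 100% |
| 20% | 50% | 99.8% |
| 10% | 13% | 77% |

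Formula check for the lowest cell (k = 0.1, ρ = 0.5): P = 2.01, b = 0.0498, v = 0.0050 + 0.3333 = 0.338, w = 1.990, SE = 0.0414, b/SE = 1.20, rejection 15%. A second simulation gave about 16% there and 53% at 20% remaining.

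**Effect of the end-of-PPCI covariate.** When arrival acts on later values only through the measured end-of-PPCI value, the test rejects in 2.4 to 2.6% of trials with that covariate and 99.6 to 100% without it. A real dependence on arrival would then be missed.

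**The obvious repair fails.** Change from arrival tested against zero rejected in 96 to 100% of trials with equal absolute inhibition (ρ = 0.5 to 0.8), in the opposite direction, because of regression to the mean.

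**The case against.** The strongest reply is that the protocol uses inhibition for a state reached on treatment, not a fall from arrival. Low platelet response is defined by the on-treatment ADPtest result, the Background asks whether adequate inhibition is reached by the time bivalirudin stops, and the primary outcome is platelet function itself. If less inhibition means a higher on-treatment level, regressing the later level on the arrival level fits the objective. This stands as a possible reading, and it rules out saying that the protocol defines inhibition as a fall. But the objective does not state it, so its wording still needs to change, and the end-of-PPCI covariate remains a problem on either reading.

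A reader might infer that the test will be positive whether the hypothesis is true or false. The figures do not support that. Under equal percentage inhibition rejection falls to about 15% in the least favourable case, and to the nominal level if arrival acts only through the end-of-PPCI value.

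A reader might also infer that any observed slope between 0 and 1 proves more absolute inhibition in patients with high arrival values. It does not, because error in the arrival value dilutes the slope: exactly equal absolute inhibition gave average slopes of 0.50 to 0.80 without the end-of-PPCI covariate.

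Finally, the protocol leaves detail to an SAP that is not shown. The outcome, covariates and tested predictor are nevertheless already fixed in the Analysis plan. The zero null is the natural reading of a test of effects, though still a reading.

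**Conclusion.** The mismatch is real. As written, a significant arrival coefficient cannot be reported as less inhibition, because the test rejects far above 2.5% under equal inhibition in most settings examined: about 99.7 to 100% for equal absolute inhibition at correlations of 0.5 to 0.8 (about 60% at 0.2), and about 15 to 100% for equal percentage inhibition with 10 to 50% of activity remaining and arrival reliability 0.5 to 0.8. The remaining fractions and the reliability are assumptions; the direction of the problem does not depend on their exact values. It would be too strong to say that the protocol tests the wrong hypothesis on every reading, since a level-based meaning is possible but unstated. The end-of-PPCI adjustment means that, on either reading, the coefficient is not the whole arrival effect over the first 24 hours.

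**What to change.** Choose one of two courses, in the protocol or before the SAP is approved.

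1. Reword the secondary objective, and the conclusion to be drawn from it, as higher residual (on-treatment) platelet activity in patients with high arrival activity. This agrees with the level-based definition of low response. Test predictor (b) in a model without the end-of-PPCI value.
2. Keep inhibition and define its scale in advance. Test against the slope that means equal inhibition: 1 on the raw scale for absolute inhibition, or 1 on log-log for percentage inhibition. Leave out the end-of-PPCI value and correct for error in the arrival value, since an uncorrected slope is pulled below 1. The duplicate readings that the protocol intends to analyse capture assay error only, not sampling or short-term biological variation, so a sensitivity range for reliability is needed.

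Do not substitute simple change from arrival tested against zero. Whether the end-of-PPCI value stays in the test of door-to-balloon time is a separate decision.

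Both courses use the data already planned. The first costs only wording and a second model fit. Under the second, the test is less likely to be significant and its confidence interval is wider.
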